### Outcome measures and instruments

#### Quantitative assessments

We will collect data on demographic characteristics (gender, age, ethnicity), level of intellectual disability and adaptive behaviour at baseline. The latter two will be assessed by the Wechsler Abbreviated Scale of Intelligence (WASI) [34] and the short version of the Adaptive Behaviour Scale [35] respectively. Cause of learning disability will be recorded if known.

#### Primary outcome measure

Changes in challenging behaviour as measured by the Aberrant Behaviour Checklist [36,37] over 12 months. The instrument has been widely used for monitoring changes in behaviour in people with intellectual disability following treatment and has demonstrated acceptable reliability and validity. The ABC scores can be separated into five different factors comprising (I) Irritability, Agitation, Crying (15 items), (II) Lethargy, Social Withdrawal (16 items), (III) Stereotypic Behaviour (7 items), (IV) Hyperactivity, Non-compliance (16 items), and (V) Inappropriate Speech (4 items). Each domain is rated on a four point scale (0–3). A total score can be obtained by adding up all domain scores. It will be completed by the person’s paid or family carer at all time points.

#### Secondary outcome measures

Mental health and autism spectrum disorders will be assessed by the mini version of the Psychopathology Assessment Scale for Adults with Developmental Disability (mini PASADD) [38]. It is administered by trained professionals to family and/or paid carers and to the service user where possible. The instrument comprises 86 psychiatric symptoms with threshold scores for the following psychiatric disorders: Depressive Disorder, Anxiety Disorder, Hypomania/Mania or Expansive mood, Obsessive Compulsive disorder, Psychosis, Dementia or Unspecified Disorder and a screen for pervasive developmental disorder. The latter will be administered once at baseline.

EuroQol Youth (EQ-5D-Y) will be used to calculate Quality Adjusted Life Years (QALYs) in line with accepted guidance [39]. The EQ-5D-Y is a 5 domain (usual activity, self-care, mobility, pain and anxiety/depression), 3 level (no problems, some problems and extreme problems) questionnaire. It will be administered at all time points.

Community participation will be assessed with the Guernsey Community Participation and Leisure Activities Scale (GCPLAS) [40]. It was developed to monitor the impact of interventions on the service user’s daily living. It contains six categories of activity that refer to 49 operationally defined contacts. The frequency of participation over the previous six month period is rated on a five point scale. It will be administered at all time points.

Family carer burden will be measured by the Uplift/Burden Scale [41], a 23-item scale that has six uplift and 17 burden items. The scale has previously been used in this population (6). It will be administered at all time points.

Family carer psychiatric morbidity will be measured by the GHQ12 [42].

Paid carer burden will be measured by the Caregiving Difficulty Scale-Intellectual Disability (CDS-ID) [43]. It is adapted from an existing scale and measures subjective burden. It will be administered at all time points.

Costs of care will be collected using a modified version of Client Services Receipt Inventory (CSRI) for people with intellectual disability [44]. It will be administered at all time points for the preceding 6 months.

Use and/or change of all medications will be recorded during the study period.

### Qualitative component

We will carry out audiotaped interviews of i) a purposive sample of 15 staff that have undergone training in PBS to explore their views on the training and challenges they faced by taking part in the study; ii) all service managers in order to explore their viewpoint in terms of the impact of the training on the service and the practices that may underpin service response to challenging behaviour; iii) up to 15 paid and 15 family carers for their views and experiences of having been allocated to the intervention arm; iv) up to 15 service users who have experienced the intervention. We will develop a semi-structured interview schedule with the help of both paid and family carers and service users. It will be applied flexibly and may be modified in order to be responsive to emergent themes. If the intervention is shown to be effective, this data will inform the scaling up of the intervention across community intellectual disability services in the UK. If it is ineffective, the data may give some indication of where and why it failed.

### Process evaluation

We will develop a checklist specifically for the study to monitor treatment fidelity. It will ask professionals delivering the intervention to rate whether or not essential tasks were carried out in sessions (adherence) on a yes/no rating. It will also contain a section for comment and to rate whether the treatment goals were achieved by the final session. Furthermore, the list of topics for discussion in supervision sessions with trainers will be available as a record of any issues arising during the trial. Samples of behavioural plans will be checked by the training team as well as an independent advisor to ensure that the quality of the assessments is maintained throughout the trial. Finally we will collect information regarding the resource implication for delivering the intervention in terms of staff time spent in training, supervision or travelling.

### Statistical analysis

We shall follow CONSORT guidelines for the analysis of cluster randomised trials and reporting of findings (http://www.consort-statement.org/).

The baseline characteristics of the PBS and TAU groups will be summarised using means, standard deviation and proportions as appropriate. A three level regression model adjusting for baseline ABC measurements, time period and effects of clustering by services and accounting for repeated measures within subjects will be used for the primary analysis. Similar analyses will be conducted for the secondary outcomes using appropriate regression models depending on the type of outcome. Results from all secondary analyses will be presented as estimates with confidence intervals and treated as exploratory. If we encounter missing data, bias due to missing data will be investigated initially by comparing the characteristics of the trial participants with complete follow-up measurements and those who have incomplete follow-up or no outcome data, descriptively. If differences are observed in the participants’ characteristics in the descriptive analysis, factors which are likely to be associated with the outcome will be included in a multilevel logistic regression analysis (with missing yes or no as outcome) to identify predictors of missing data. If predictors associated with both missing data and the outcomes are found, these will be included in the multilevel models examining the effects of intervention on the outcomes [45]. A sensitivity analysis will also be carried out to examine the effect of PBS on ABC score after adjusting for area deprivation and the service staff to patient ratio if appropriate. Multiple imputation may be used as part of the sensitivity analysis accounting for the clustered nature of the data if considered appropriate [46-48]. As part of the sensitivity analysis we will also examine intervention by time period interaction. All analyses will be carried out on an intention to treat basis. A detailed statistical analysis plan will be agreed by the Trial Steering Committee prior to the analysis of unblinded data.

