### Sample size

The primary outcome is the total Aberrant Behaviour Checklist (ABC) score measured repeatedly at six and 12 months following recruitment. The pilot study [15] generated mean baseline ABC scores of 45.4 (SD 26.4). A reduction of 0.45 of a standard deviation on the ABC score in the ABC group compared to the TAU group is considered to be clinically important. Using an analysis of covariance approach based on a correlation of 0.48 between the baseline and post-intervention ABC measurements (as per pilot study, 15) 80 patients per arm will be required to detect a difference of 0.45 SD with 90% power and 5% significance level. Inflating for clustering within the community intellectual disability services, using the formula proposed by Eldridge et al. [31] which accounts for variable cluster sizes and an intracluster correlation of 0.062 (estimated from the pilot study), an average cluster size of 12 (we expect it to be 13, however, allowing for 10% attrition and rounding it up to the nearest integer we have used a cluster size of 12 in our calculations), and a standard deviation for the cluster size of 3, a total of 276 patients will be required. However, this sample size can be reduced as each patient will provide two measurements of ABC score. Using a correlation of 0.6 between the 6 and 12 months post intervention ABC measurements (15,16) and a cluster size of 2, a total of 442 ABC measurements from 221 patients will be required. In performing this calculation we have assumed that there will be no treatment by time period interaction over 12 months supported by the pilot studies [11,12]. To allow for 10% attrition over the 12 month period a total of 246 patients will be recruited to the trial thus requiring 19 clusters. The sample size calculation is based on the program and formulae in STATA version 12.

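### The sample size makes no allowance for having only 19 randomised services: on the plan's own formula, power at a valid 5% level is about 86%, not 90%

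*Protocol article*

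**What the plan says.** The Trial design section makes the community intellectual disability service the unit of randomisation, and the Randomisation section sets 1:1 allocation.

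The Sample size section starts from individuals: "80 patients per arm will be required to detect a difference of 0.45 SD with 90% power and 5% significance level", with an ANCOVA reduction "based on a correlation of 0.48 between the baseline and post-intervention ABC measurements". It then inflates for clustering with "an intracluster correlation of 0.062 (estimated from the pilot study"), "an average cluster size of 12 (we expect it to be 13" before attrition) and a cluster-size SD of 3, which gives 276. A correlation of 0.6 between the two follow-ups brings this down to 221 patients. Ten per cent attrition brings it up to 246, "thus requiring 19 clusters".

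The Statistical analysis section names the primary model: "A three level regression model adjusting for baseline ABC measurements, time period and effects of clustering by services", also accounting for repeated measures within subjects. It does not say whether the fit is ML or REML, or against which distribution the treatment effect is tested. It refers detail to a statistical analysis plan that is not shown.

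**The concern.** In a cluster randomised trial the precision of the treatment contrast is limited by the number of clusters. With 19 services in two arms, about 19 - 2 = 17 degrees of freedom are available to estimate between-service variation. The design effect inflates the variance of the contrast, but it does not allow for that variance being estimated from few units. A sample size built on normal quantiles therefore overstates the power of a test that holds its nominal level.

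The consequence falls on the single primary test, because the secondary analyses are declared exploratory. If the test is valid at 5%, the chance of missing the planned effect is larger than the stated 10%. If the test uses the normal distribution, the 5% level is exceeded and the confidence interval is too narrow.

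**Working it through.** **Inputs, all from the Sample size section unless noted**
- Effect 0.45 SD, 5% significance, 90% power. Sidedness is not stated; two-sided reproduces the figure.
- Baseline to follow-up correlation 0.48.
- Intracluster correlation (ICC) 0.062; mean cluster size 12 analysed (13 recruited), SD 3, so the coefficient of variation is 3/12 = 0.25.
- Correlation between the 6- and 12-month scores 0.6.
- 221 analysed, 246 recruited, 19 services. With 1:1 allocation that is 9 against 10.

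**Step 1: reproduce the plan**
- Per arm: 2 × (1.96 + 1.2816)² / 0.45² × (1 - 0.48²) = 79.9, rounded to 80.
- Design effect: 1 + [(1 + 0.25²) × 12 - 1] × 0.062 = 1.7285.
- Clustered total: 2 × 79.87 × 1.7285 = 276.1, stated as 276.
- Two follow-ups: (1 + 0.6)/2 = 0.8; 276 × 0.8 = 220.8, i.e. 221.
- Attrition: 221/0.9 = 245.6, i.e. 246. Services: 246/13 = 18.9, i.e. 19.

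Every figure reproduces with normal quantiles. No step allows for the number of services.

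**Step 2: power on the plan's own variance**
- SE = √(4 × 0.7696 × 0.8 × 1.7285 / 221) = 0.1388, where 0.7696 = 1 - 0.48².
- Noncentrality = 0.45 / 0.1388 = 3.242.
- Normal reference (critical value 1.96): power 90.0%, so there is no slack.
- t on 17 df (critical value 2.110), noncentral t: power 86.3%.
- t on 15 df (two further service-level covariates): 85.7%.
- t on 17 df with all 19 services yielding 12 analysed (228 patients): 87.3%.

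**Step 3: sensitivity to how the variance is read (t, 17 df, 221 patients unless noted)**

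The plan multiplies the whole variance by 0.8, so it treats service-level variance as shrinking when two visits are averaged.

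| Reading | Power |
|---|---|
| Service variance kept at 0.062 × 0.7696 = 0.0477; patient-mean variance 0.8 × 0.7696 = 0.6157; ICC of the mean 0.0775; design effect 1.911 | 82.8% |
| Service variance 0.0477; patient-mean variance 0.8 - 0.48² = 0.5696; ICC 0.0838; design effect 1.984 | 84.2% |
| ICC applied to total variance: 0.062/0.5696 = 0.1088; design effect 2.279 | 79.0% |
| Patient-mean variance 0.5696, ICC left at 0.062, design effect 1.7285 | 88.8% |
| As the previous row, with design effect 1.708 for an inverse-variance-weighted model and 228 patients | 90.0% |

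**Step 4: check by simulation**

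A random-intercept model was fitted to participant means (both follow-ups present), with 19 services split 9 and 10 and service sizes averaging 11.6 analysed (SD 3). There were 10,000 null and 5,000 alternative trials per setting. With the plan's variance scaling, REML with t on 17 df had type I error 4.6% and power 86.4%; a t test on service means had 4.8% and 85.9%.

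**Step 5: type I error if the normal distribution were used**
- By formula: P(|t₁₇| > 1.96) = 6.66%.
- By simulation: 6.2-6.4% with REML and 7.5-8.1% with ML in the settings above. A further set of 20,000 null trials per setting (ICC of the participant mean 0.062 to 0.109) gave 6.6-6.8% with REML and 7.8-8.3% with ML.

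**The case against.** A reader might infer that the primary analysis itself is anti-conservative, with a type I error of 6.6-8%. The article does not support that. It never commits to Wald or normal-based inference or to ML, and it leaves such detail to an analysis plan that is not shown. The absence of a degrees-of-freedom method from a protocol article is no finding. The inflated error rate belongs to one possible choice of test, and the 8% end needs ML as well.

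A reader might also infer that 5% and 90% can never hold together. That is too absolute. The plan's formula is itself approximate. Taking the adjusted patient-mean variance as 0.8 - 0.48², using the smaller design effect of a weighted mixed model and counting 228 analysed patients brings power on 17 df to 90.0%. That result needs all three favourable re-readings together, leaves the formula the plan used, and still lets service-level variance shrink when visits are averaged. Without that shrinkage power falls below 86%, so the approximations act in both directions.

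The point about scale also stands. The loss is 90.0 - 86.3 = 3.7 points, within what a different ICC would do: on the plan's formula with t on 17 df, power is 90.3% at an ICC of 0.044, 89.0% at 0.050 and 82.2% at 0.080. That makes the point modest. It does not make the stated 90% correct on the plan's own inputs.

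**Conclusion.** The point holds as a modest error in a headline design figure. On the plan's own inputs and variance steps, a test that holds the 5% level has about 86% power with 19 services, so the risk of missing the planned effect is about 14% instead of 10%. The plausible range is about 83-84% if service-level variance is not reduced by averaging visits, up to about 89-90% on the most favourable readings; applying the ICC to total variance would take it to about 79%.

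This rests on 17 between-service degrees of freedom, a two-sided test, and the plan's effect size, correlations and ICC taken as given. The simulations also assume both follow-ups are present for each analysed patient. The type I error of about 6.7% (REML; higher with ML) is conditional on a normal reference distribution, which the article neither states nor excludes.

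**What to change.** In the Sample size section, restate the power as about 86% at a valid 5% level with 19 services on the plan's own formula, and say that this allows for about 17 between-service degrees of freedom.

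In the Statistical analysis section, or in the analysis plan if it does not already say so, add one sentence: the three-level model is fitted by REML, and the treatment effect and its interval use a small-sample correction (Kenward-Roger, Satterthwaite, or services minus 2 degrees of freedom).

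The cost is a less favourable quoted power and an interval about 8% wider than a normal-based one (2.110/1.960 = 1.076). No extra patients are requested. For information, at the same number of patients per service the plan's formula gives 89.8% with 21 services and 91.3% with 22, should the sponsor prefer to keep the 90% claim.

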#### Secondary objectives

i.To compare the costs of care in each arm.ii.To examine the impact of the intervention and TAU at 12 months on prescription of psychotropic medication, burden on family and paid carers, service user mental status, and participation in community-based activities compared to TAU alone.iii.To carry out an exploratory analysis of the impact of the intervention and TAU alone at 12 months on all measures in a sub-sample of participants with autism spectrum disorders (ASD).iv.To measure the influence on the primary outcome of level of intellectual disability, mental status and ASD status and adaptive behaviour scores.

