### Randomisation

Once the services have been recruited, randomisation will be performed using a web based randomization system which uses random permuted blocks on 1:1 allocation. Although originally we had discounted minimisation given the lack of good evidence for the impact of various variables on patient outcomes, given the variation in cluster sizes we will use the following data in our randomisation planning: team size (number of full time equivalent staff), in or out of London, number of service users registered per team. We have calculated the ratio of staff:patient in and out of London teams and in order to account for the variation we will stratify the teams by a binary factor to indicate whether a team is below or above a median ratio. Randomisation will take place after the participants have been screened for eligibility and consented to the trial. Baseline data collection will follow.

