### Possible sources of bias

One potential source of bias is transfer of trained staff between trained and control teams during the trials. We have examined the turnover of health staff in a number of services which have expressed interest in participating and this is well below 13% which is considered very low based on National Health Service performance data. Furthermore contamination between study arms is unlikely given the more intensive nature of the intervention. However, PBS principles are being taught widely therefore, some knowledge of PBS will be unavoidable. We will collect information from all participating teams on the level of knowledge and training the staff may have had in delivering any aspects of PBS. Another potential source of bias may derive from variation in patient characteristics between teams. However, we do not anticipate substantial variation in this respect as the teams will cover diverse geographical areas thus reducing the possibility of bias.

Selection bias resulting from recruiting participants after cluster allocation has been revealed will be avoided by completing recruitment and screening assessment prior to randomisation.

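### The primary model adjusts for baseline ABC and time period only and forgoes a modest, nearly free gain from patient-level traits that the trial already collects

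*Protocol article*

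**What the plan says.** Under Statistical analysis, the primary analysis is "A three level regression model adjusting for baseline ABC measurements, time period and effects of clustering by services", also accounting for repeated measures within subjects. Two other routes to adjustment appear there. A sensitivity analysis estimates the effect on ABC "after adjusting for area deprivation and the service staff to patient ratio if appropriate". Separately, if characteristics are found that predict both missing data and outcome, "these will be included in the multilevel models examining the effects of intervention on the outcomes".

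Secondary objective iv reads "To measure the influence on the primary outcome of level of intellectual disability, mental status and ASD status and adaptive behaviour scores". Outcome measures and instruments shows that the data will exist: level of intellectual disability (WASI) and the short Adaptive Behaviour Scale are taken at baseline, and the mini PASADD supplies mental status and a one-off screen for pervasive developmental disorder.

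Randomisation is by service. The article says "we will stratify the teams by a binary factor to indicate whether a team is below or above a median ratio", the ratio being staff to patients. No patient characteristic enters the allocation. Possible sources of bias names variation in patient characteristics between teams and then sets it aside: "we do not anticipate substantial variation in this respect as the teams will cover diverse geographical areas thus reducing the possibility of bias".

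**The concern.** With 19 services, about nine or ten per arm, randomisation leaves room for the arms to differ by chance in patient mix. Three of the listed factors are patient-level traits that could be entered in the primary model at almost no cost, and they are not.

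The one reason given for setting patient mix aside does not work. That teams cover diverse areas is no reason to expect their patients to be alike; if anything it points the other way. The article also reasons differently in its Health economic evaluation: because baseline utility is not controlled at randomisation and may differ between arms, regression will adjust for it. The same holds for the traits in objective iv.

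At stake is some precision in the primary estimate, and how easily a reader could attribute part of that estimate to a visible difference in case mix.

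**Working it through.** **Inputs from Sample size.** Difference 0.45 SD, power 90%, significance level 5% (taken as two-sided), baseline/follow-up correlation 0.48, ICC 0.062, mean cluster size 12 (13 recruited) with SD 3, correlation 0.6 between six and 12 months, attrition 10%, ABC SD 26.4.

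**The plan's own figure.**
- Per arm: 2 × (1.960 + 1.282)² / 0.45² × (1 − 0.48²) = 103.8 × 0.7696 = 79.9, so 80.
- Design effect with CV 3/12 = 0.25: 1 + ((0.25² + 1) × 12 − 1) × 0.062 = 1.7285. From the unrounded per-arm size, 2 × 79.87 × 1.7285 = 276.1, so 276.
- Two measurements: 276 × (1 + 0.6)/2 = 220.8, so 221.
- Attrition: 221/0.9 = 245.6, so 246. Clusters: 246/13 = 18.9, so 19.

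The chain reproduces with baseline ABC as the only prognostic covariate. The stated 90% power therefore does not rely on any further adjustment.

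**Gain from further covariates.** The planned standard error is 0.45/(1.960 + 1.282) = 0.139 SD. Let R² be the share of residual variance that the added covariates explain, applied equally at patient and team level. The documents give no value, so R² is an assumption. The standard error scales by √(1 − R²), power is Φ(3.2415/√(1 − R²) − 1.960), and the analysed number needed for 90% power is 221 × (1 − R²).

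| R² (assumed) | SE change | Power | Patients needed for 90% |
|---|---|---|---|
| 0 | none | 90.0% | 221 |
| 2% | −1.0% | 90.6% | 217 |
| 5% | −2.5% | 91.4% | 210 |
| 10% | −5.1% | 92.7% | 199 |
| 20% | −10.6% | 95.2% | 177 |

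**Chance imbalance.** For one standardised patient covariate among 246 patients in clusters of 13 (SD 3), the SD of the arm difference is √(4 × D/246), with D = 1 + (13 × (1 + (3/13)²) − 1) × ICC. The covariate's ICC is an assumption. It gives 0.128 at ICC 0, 0.163 at 0.05 and 0.192 at 0.10.

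Take ICC 0.05 and an assumed slope of 0.2-0.3 SD of follow-up ABC per SD of covariate, given baseline ABC.
- A typical (one-SD) imbalance moves the estimate by 0.163 × 0.2 to 0.163 × 0.3 = 0.033-0.049 SD. That is 7-11% of the 0.45 SD target, or about 0.9-1.3 ABC points against 11.9.
- The 1-in-20 imbalance, 1.96 × 0.163 = 0.32 SD, moves it by 0.06-0.10 SD, or 14-21% of the target. This is roughly 0.5-0.7 of the planned standard error.

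**These are one effect, not two.** A slope of 0.2-0.3 corresponds to 0.04-0.09 of total variance, and 0.04/0.7696 to 0.09/0.7696 is 5-12% of residual variance. That is essentially the 5-10% used for the precision gain. The shift and the wider standard error are two views of the same sampling variance and must not be added.

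**The case against.** The strongest reply is that nothing in the stated model is wrong. Adjusting for baseline outcome, time and clustering is a valid, prespecified analysis. Chance imbalance under randomisation is sampling variation that the standard error already reflects. This stands in full. A reader might infer that the primary estimate is biased or the trial underpowered; the documents support neither.

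A reader might also infer that the plan contradicts itself by expecting these factors to be prognostic and then omitting them. It does not. Objective iv sets out only to measure their influence, secondary analyses are labelled exploratory, and Randomisation explains that minimisation was first discounted "given the lack of good evidence for the impact of various variables on patient outcomes". The factors are possible influences, no more.

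Nor is patient mix left wholly unaddressed. Baseline ABC will absorb part of it, and predictors of missingness may enter the models. But the named sensitivity analysis covers deprivation and staffing, not patient traits, and only if judged appropriate. The missingness route makes the covariate set depend on observed dropout. Neither replaces a fixed list. Whether the stratification factor itself belongs in the primary model is a separate question.

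The ICC of 0.062 describes the ABC outcome, not patient mix, so it does not show that teams differ in these traits. No stated analysis depends on the sentence about diverse areas; it is poor reasoning, not a design fault.

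Finally, the article promises a detailed analysis plan, not shown here, which may list more covariates. That is a fair caution. Still, the article does state the primary model's adjustment, and this point addresses what it states.

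**Conclusion.** The point holds as an improvement to a sound analysis. The stated primary model leaves out patient-level traits that the trial collects and itself singles out for study, and randomising 19 services does not balance them. If the traits explain 5-10% of residual variance, using them would cut the standard error by about 2.5-5% and raise power from 90% to about 91-93%. At 2% the gain is negligible; at 20% it would be substantial. Nothing in the documents fixes where the truth lies. The 14-21% shift is a 1-in-20 case under assumed slope and ICC, and is not a harm additional to the precision figure. The case for the change is that the benefit, though modest, costs almost nothing and the covariate set would no longer depend on what is observed.

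**What to change.** Name level of intellectual disability, adaptive behaviour score and ASD screen result as fixed covariates of the primary three-level model, included whatever imbalance or dropout is seen. Keep the model with baseline ABC and time period alone as a sensitivity analysis.

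Leave baseline mental status out of the primary set unless it was recorded before allocation. Under Randomisation, baseline data collection follows allocation, and under Masking the teams are not blind. The mini PASADD draws on carers, and mental status can change, so a score taken then could be affected by knowledge of the arm. The three proposed covariates are meant as stable traits that allocation should not alter; where a value from before allocation exists, use it.

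Delete the statement under Possible sources of bias that diverse geographical areas reduce variation between teams.

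The cost is a sentence or two in the protocol or analysis plan, a few patient-level degrees of freedom, and a simple rule for occasional missing baseline values. No new data are needed for these three covariates.

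### Covariate adjustment for missing data hangs on a completer/non-completer comparison that ignores trial arm, so it can miss dropout that differs by arm; at the planned 10% attrition the resulting bias is modest

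*Protocol article*

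**What the plan says.** The Statistical analysis section of the protocol article sets out a sequence.

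1. The primary model is "A three level regression model adjusting for baseline ABC measurements, time period and effects of clustering by services", with repeated measures within participants.
2. If data are missing, "bias due to missing data will be investigated initially by comparing the characteristics of the trial participants with complete follow-up measurements and those who have" gaps in their outcome data or none at all. This comparison is descriptive, and no threshold is given.
3. If differences appear, factors likely to be related to outcome are "included in a multilevel logistic regression analysis (with missing yes or no as outcome) to identify predictors of missing data".
4. The action that follows is stated thus: "If predictors associated with both missing data and the outcomes are found, these will be included in the multilevel models examining the effects of intervention".
5. As a fallback, "Multiple imputation may be used as part of the sensitivity analysis accounting for the clustered nature of the data if considered appropriate".

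Trial arm is not mentioned in steps 2 to 4. The section then defers detail: "A detailed statistical analysis plan will be agreed by the Trial Steering Committee prior to the analysis of unblinded data".

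Two other places matter. The Sample size section says: "To allow for 10% attrition over the 12 month period a total of 246 patients will be recruited to the trial thus requiring 19 clusters". Secondary objective iv reads "To measure the influence on the primary outcome of level of intellectual disability, mental status and ASD status and adaptive behaviour scores", so the plan already names four characteristics that it expects may influence the primary outcome.

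**The concern.** The stated purpose of the screen is to detect bias from missing data. What matters for the trial's conclusion is bias in the PBS minus TAU contrast. That arises when dropout changes the mix of participants differently in the two arms, not merely when dropouts differ from completers overall.

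Dropout that differs by arm is plausible here. Teams are not masked, carers complete the Aberrant Behaviour Checklist (ABC), and one arm receives an intensive intervention. If participants with a given characteristic leave more often under PBS and less often under TAU, the two patterns tend to cancel when arms are combined. The characteristic then looks unrelated to dropout, and it stays out of the effect models although it is biasing the contrast.

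Two further weaknesses follow from making adjustment conditional. Few dropouts are expected, so an absence of visible difference is weak grounds for leaving a factor out. The covariates of the primary model also come to depend on the observed data, including the outcomes.

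**Working it through.** **The plan's own figures.** All inputs are from the Sample size section.
- Per arm: 2 × (1.960 + 1.282)² × (1 − 0.48²) / 0.45² = 79.9, so 80.
- Design effect, with coefficient of variation 3/12 = 0.25: 1 + ((0.25² + 1) × 12 − 1) × 0.062 = 1.7285. Then 160 × 1.7285 = 276.6 (stated: 276).
- Two measurements: 276 × (1 + 0.6)/2 = 220.8, so 221. Attrition: 221/0.9 = 245.6, so 246. Clusters: 246/13 = 18.9, so 19.

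The chain reproduces. Expected dropouts are 246 − 221 = 25. The target is 0.45 × 26.4 = 11.9 ABC points.

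**What drives the bias.** Take a standardised baseline factor X. Let b be its log-odds of dropout per SD, p the dropout rate, and w its effect on outcome (in outcome SD per SD of X) beyond baseline ABC. To first order, the mean of X among those observed shifts by −b × p. In a linear outcome model without X, the size of the bias in the contrast is therefore about

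w × |b(PBS) × p(PBS) − b(TAU) × p(TAU)|.

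A screen on both arms combined responds instead to the information-weighted average of the two slopes. With 246 participants and 10% missing, the standard error of that slope is about 1/√(246 × 0.1 × 0.9) = 0.213.

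**Assumptions not in the documents.** w = 0.4; b as shown in the table; p < 0.05 standing in for the unstated threshold. The simulations used 19 teams of about 13, ICC 0.062, baseline correlation 0.48 and one follow-up visit, with 3,000 trials per scenario. Ranges are across repeated runs.

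| b in PBS / TAU; missing in PBS / TAU | Bias by formula (SD) | z = average slope / SE | Screen fires: approximation | Screen fires: simulation | Bias left after the rule (SD) |
|---|---|---|---|---|---|
| 0.5 / 0.5; 10% / 10% | 0 | 0.5/0.213 = 2.35 | 65% | 63–66% | 0 |
| 0.5 / 0.5; 15% / 5% (or reversed) | 0.4 × (0.075 − 0.025) = 0.02 | 0.5/0.215 = 2.32 | 64% | 59–64% | about 0.01 |
| 0.5 / 0; 10% / 10% | 0.4 × 0.05 = 0.02 | 0.25/0.213 = 1.18 | 22% | 20–25% | 0.015–0.018 |
| 0.5 / −0.5; 10% / 10% | 0.4 × 0.10 = 0.04 | 0 | 5% | 6–7% | 0.037–0.038 |
| 1 / −1; 10% / 10% | 0.4 × 0.20 = 0.08 | 0 | 5% | 10–11% | 0.06–0.09 |

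With X always in the model, bias is about 0 in every row and the SD of the estimate is about 5% lower. At 20% missing, twice the planned attrition, slopes of 0.5 and −0.5 give 0.4 × 0.20 = 0.08 SD, and the screen fires about 6% of the time.

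**Second set-up.** This used no clustering, dropout odds ratios of 2 or 3 per SD, and partial correlations with outcome of 0.3 or 0.5, at about 10% attrition overall.
- Opposite slopes, equal dropout: bias 0.9 to 2.3 ABC points (8–19% of 11.9; at most 0.09 SD); screen fires 7–10%.
- Slope in one arm only: bias 0.5 to 1.6 points; screen fires 34–89%.
- Equal slopes, dropout 5% and 15%: bias 0.4 to 1.1 points; screen fires 86–100% and leaves a bias of about 0.

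**Sensitivity of the screen.** For 25 dropouts against 221 completers, the standard error of a standardised difference is √(1/25 + 1/221) = 0.211. A true 0.5 SD difference gives z = 0.5/0.211 = 2.37, hence power of 66% at the 5% level. It would be missed 34% of the time.

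**The case against.** **The screen often works.** A reader might infer that it mostly fires when there is no bias and misses bias when it exists. The calculations do not support that. With equal slopes and unequal dropout it usually fires and removes about half to nearly all of the bias. With a strong predictor in one arm it often fires. The near-total miss is confined to slopes that roughly cancel. Firing without bias does no harm, because the added factor is prognostic and improves precision. This stands.

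**The tested rule is not the stated rule.** The first step is descriptive, so a significance test is only a stand-in. If a difference above 0.2 SD counted (also an assumption), that step would fire about 57–62% of the time in the one-arm case and 37–38% with opposite slopes. This stands as a limit on the firing rates. It does not rescue the screen for opposite slopes: an unrelated factor would exceed 0.2 SD by chance about 34% of the time (z = 0.2/0.211 = 0.95).

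**Pooling is not explicit.** The article does not say that arms are pooled, and it does not exclude an arm term from the logistic model. That is correct. Pooling is the natural reading, and the descriptive comparison that opens the way to the logistic model makes no reference to arm.

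**Other protection exists.** Multiple imputation is not the only other safeguard: the primary model adjusts for baseline ABC and uses both visits, so participants seen only at six months still contribute. This stands, and it means that the one-visit calculations may overstate the bias.

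**An arm-by-factor test is not a better gate.** In the second set-up it fires only 4–5% of the time with equal slopes and unequal dropout, where the contrast is biased. This is right, and it argues for dropping the gate for known prognostic factors, not for replacing it.

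**This is detail for the analysis plan.** That plan is not shown and may deal with the point. But the article states a specific rule, so the question is how that rule is fixed and not whether detail is absent. Adding predictors of both missingness and outcome is a sound missing-at-random step; the weak part is making it conditional on a screen that does not look by arm.

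**Conclusion.** The point holds as a modest weakness in a stated rule. The effect models are adjusted only if a screen fires, and the screen as described does not examine the condition that biases the PBS minus TAU contrast. It can miss dropout that differs by arm, it has limited sensitivity with about 25 dropouts, and it lets observed data choose the primary model's covariates.

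At the planned 10% attrition, bias is about 0.02 to 0.04 SD (0.5 to 1.1 ABC points, 4–9% of the 0.45 SD target) for a moderately strong factor. It stays just under 0.1 SD in extreme opposite-slope cases. These sizes rest on assumed strengths for the factor's link with dropout and outcome, on a p < 0.05 stand-in for the screen, and on one follow-up visit. The documents do not show that the trial's result would be materially biased, nor that the screen fails in general.

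**What to change.** In the analysis plan:

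1. Prespecify the four baseline factors of secondary objective iv (level of intellectual disability, adaptive behaviour, autism spectrum disorder status and baseline mental status). Include them with baseline ABC in the multilevel models whatever the screen shows. Mental status must be the baseline value, since it is also followed as an outcome.
2. Report dropout, and the comparison of completers with non-completers, separately by arm.
3. Keep the protocol's provision to adjust for any further predictor of both missingness and outcome, and report the effect estimate with and without such predictors. Confining them to a sensitivity analysis would be debatable, because the primary estimate could then stay biased where the present rule would adjust it.

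The cost is wording and a few participant-level degrees of freedom; no new data are needed. If the factors are prognostic, precision improves slightly: the standard error falls by about 5% at an outcome weight of 0.4 SD per SD, and by about 1% at 0.2.
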